### Adverse events

Adverse events included medical or surgical complications occurring within six months after index TKA. The clinician investigators on the AViKA team ascertained the seriousness of each adverse event and whether it was related to the trial. Adverse events were reported to the Partners IRB per IRB policies.

### Sample size and power

The principal outcome measure was the difference between arms in functional improvement as measured by the difference in the WOMAC function scale from baseline to six months. The sample size considerations were based on the ability of the study to detect a ten point difference between the care navigator and usual care arms. This difference is approximately one half of the standard deviation of change noted in observational pilot data. It is also in the range of the minimal clinically important difference in the WOMAC function scale among OA patients estimated by Angst et al.
[15,16]. We adopted a Type I error rate of 5% and power of 80%. The sample size calculation took into account losses to follow-up, which we estimate at approximately 10% based on pilot data. We powered the study for one pre-planned subgroup analysis in which obese patients will be compared to non-obese patients via formal testing of the statistical significance of a multiplicative interaction between the intervention effect on obese and non-obese TKA recipients. On the basis of these considerations, we set the target sample size at 300 patients. With an anticipated 10% attrition rate we plan to enroll 345 subjects.

### Analytic approach

The primary analysis will be a comparison of six month changes in WOMAC function score between the care navigator and the usual care groups, using the “intention to treat” approach, in which subjects are analyzed in the group to which they were randomly assigned. We will also perform a secondary “intention to treat” analysis in which the dependent variable is a failure indicator defined as failing to achieve a minimal clinically important improvement in WOMAC function score (one half of the standard deviation)
[15,16]. This analysis provides an estimate of efficacy at the level of the subject rather than the group. We will perform additional exploratory analyses to identify factors associated with outcome, including preoperative functional status and pain, catastrophizing, self-efficacy, and depression, as per prior literature
[3-7]. If the intervention is associated with improvements in functional outcome, we will use general linear models to determine whether intervention effects are mediated by improvements in self-efficacy or catastrophizing.

In addition, a formal economic analysis is planned to determine the cost-effectiveness of the care navigator intervention as compared with usual care. The analysis will incorporate accepted principles of cost-effectiveness analyses including a societal perspective and discounting of all costs and health benefits
[17].

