#### Randomization

After surgery, patients were randomized to one of the two treatment arms, enhanced postoperative care (navigator arm) or usual care. The randomization schedule was stored in a password protected file, accessible only to the study data manager ([name]). Patients were randomized by the data manager ([name]) the day after surgery in the order in which surgery was completed. We used randomly varying permutated blocks with varying block sizes to randomize patients within 8 strata. The strata included age (<65 vs. 65+), sex, and surgeon (high volume vs. low volume). Please refer to Figure 
1 for a visual representation of the two study arms.

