### Outcome measures

The primary outcome of the study was the difference between the two arms in functional improvement from preoperative (baseline) status to six months postoperatively, as measured by the difference in Western Ontario and McMaster Universities Osteoarthritis Index (WOMAC) function score. Secondary outcomes included quality-of-life improvements (as measured by EuroQol) and health care services utilization over the course of three and six months postoperatively.

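### The primary analysis is stated as a comparison of six-month WOMAC changes, with no stated adjustment for baseline WOMAC or the randomization strata; specifying that adjustment would gain precision at no data cost

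*Protocol article*

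**What the plan says.** All references are to the protocol article.

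- **Outcome measures** defines the endpoint as a between-arm difference in change: "The primary outcome of the study was the difference between the two arms in functional improvement from preoperative (baseline) status to six months postoperatively".
- **Analytic approach** carries this into the analysis: "The primary analysis will be a comparison of six month changes in WOMAC function score between the care navigator and the usual care groups", by intention to treat. No test, model or covariate is named for this comparison.
- **Analytic approach** mentions baseline function once, in an exploratory role: "We will perform additional exploratory analyses to identify factors associated with outcome, including preoperative functional status and pain, catastrophizing, self-efficacy, and depression". General linear models are mentioned only for the mediation question.
- **Randomization** describes permuted blocks within 8 strata: "The strata included age (<65 vs. 65+), sex, and surgeon (high volume vs. low volume"). The analysis text does not mention these factors again.
- **Sample size and power** works on the change-score scale: "The sample size considerations were based on the ability of the study to detect a ten point difference between the care navigator and usual care". On the size of that target it adds: "This difference is approximately one half of the standard deviation of change noted in observational pilot data". It gives no baseline to six-month correlation and no residual SD. It also says the trial was powered for one obesity-by-arm interaction.

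**The concern.** A difference in changes sets the coefficient of baseline at 1. The actual regression slope of six-month score on baseline is usually something else, and then two things follow.

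First, the estimate carries avoidable variance. Second, if the arms differ by chance at baseline, the change score corrects for that difference by the wrong amount. With true slope b and observed baseline difference d, the estimate is shifted by (b − 1)d.

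The strata raise a similar issue. If age, sex or surgeon volume predict change, balancing the arms on them and then leaving them out of the model gives standard errors larger than the design warrants.

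What is at stake is the width of the primary interval and, above all, the obesity interaction. The article presents that interaction as a main question, and interactions are estimated much less precisely than main effects.

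**Working it through.** **Inputs from Sample size and power.** Difference 10 points; SD of change about 20 (10 is about half an SD); type I error 5% and power 80% ("We adopted a Type I error rate of 5% and power of 80" per cent); target 300 patients.

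**Assumptions, because the article does not give them.** Two-sided test; 1:1 allocation (Randomization says only that "patients were randomized to one of the two treatment arms, enhanced postoperative care (navigator arm) or usual care"); 300 evaluable patients; baseline to six-month correlation rho of 0.3 to 0.7; a 10-point interaction; half the patients obese.

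**Step 1: the plan's own figure.** Per arm, n = 2 × (2.8016 × 20/10)² = 62.8, so 63 per arm and 126 in total. The main effect alone therefore does not give 300. The article attributes the size partly to the interaction, but states neither the interaction's magnitude nor the obese share, so 300 cannot be reproduced.

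**Step 2: main test at 300, change score.** SE = 20 × √(4/300) = 2.309. Power for 10 points = Φ(10/2.309 − 1.96) = Φ(2.37) = 99.1%. Difference detectable at 80% power = 2.8016 × 2.309 = 6.47.

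**Step 3: effect of baseline adjustment.** With baseline SD s0 and six-month SD s1,

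Var(adjusted)/Var(change) = s1²(1 − rho²) / (s0² + s1² − 2·rho·s0·s1).

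The ratio is at most 1, and equals 1 only when the slope rho·s1/s0 is 1. With s0 = s1 it reduces to (1 + rho)/2. Holding the SD of change at 20, the residual SD is 20 × √((1 + rho)/2).

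| | Change score | rho 0.3 | rho 0.5 | rho 0.7 |
|---|---|---|---|---|
| Variance ratio | 1 | 0.65 | 0.75 | 0.85 |
| SD | 20 | 16.12 | 17.32 | 18.44 |
| 95% CI half-width, main effect (1.96 × SD × √(4/300)) | 4.53 | 3.65 | 3.92 | 4.17 |
| Detectable main effect (80%) | 6.47 | 5.22 | 5.60 | 5.97 |
| Equivalent N (300/ratio) | 300 | 462 | 400 | 353 |

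**Step 4: obesity interaction.** With a 50:50 split, SE = SD × √(16/300), twice the main-effect SE. On the change score this is 4.619, so power for a 10-point interaction = Φ(10/4.619 − 1.96) = 58.1%, and 12.9 points are detectable at 80%. After adjustment, power is 76.6%, 70.5% and 65.1% for rho 0.3, 0.5 and 0.7. The detectable interaction is 10.4, 11.2 and 11.9 points.

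**Step 5: sensitivity to unequal SDs.** Over s1/s0 from 0.8 to 1.2 and rho from 0.2 to 0.7, the variance ratio runs from 0.47 (s1/s0 = 0.8, rho = 0.2) to 0.97 (s1/s0 = 1.2, rho = 0.7). There are combinations with no gain. At rho = 0.8 and s1/s0 = 1.25 the slope is 1, and the ratio is 0.5625/0.5625 = 1.

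**Step 6: chance imbalance, one illustration.** With rho = 0.5 and equal SDs, an SD of change of 20 implies SDs of 20 at each time, so the baseline difference between arms has SE 2.31. A one-SE imbalance shifts the change-score estimate by (0.5 − 1) × 2.31, about 1.2 points in size.

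**Strata.** No stratum effects are given, so their contribution cannot be calculated.

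**The case against.** The strongest objection is that the article never says the comparison is raw or unadjusted. A linear model of change on arm with baseline as a covariate is also a comparison of changes, and it gives the same treatment estimate and standard error as a model of the six-month score on arm and baseline. A journal article commonly leaves the covariate list to the full protocol or SAP, and neither is shown. Sizing on the SD of change is a planning input and does not fix the model. Listing preoperative function among exploratory factors does not exclude it from the primary model. All of this stands. A reader might infer that the investigators decided against adjustment, but the document supports only the statement that none is stated.

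Three further objections narrow the point:

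- **Bias.** A reader might take the change score to be biased. Under randomization it is not. The shift from imbalance is conditional on the baseline difference that happens to occur, and it averages to zero.
- **Primary power.** A reader might think the primary test is endangered. At about 99% power for 10 points, it is not.
- **Size of gain.** The figures rest on a correlation, SDs, an interaction size and an obese share that the article does not supply. The loss from ignoring strata arises only if they predict change, and it errs towards conservatism, not towards excess type I error.

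The objections do not remove the point. The analysis text states a change-score contrast and gives baseline function only an exploratory place. A method that keeps the same estimand, and is at least as precise in large samples, is available from data already held.

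**Conclusion.** The point holds as a recommendation about an analysis that is valid but, as stated, probably not the most precise. The article states a comparison of changes with no stated adjustment for baseline WOMAC function or the stratification factors. It does not establish that the analysis will be unadjusted, that the estimate is biased, or that the primary hypothesis is underpowered.

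Under equal SDs and correlations of 0.3 to 0.7, adjustment cuts the variance by 15% to 35%. With SD ratios of 0.8 to 1.2 and correlations of 0.2 to 0.7, the reduction runs from about 3% to 53%. The practical return is mainly in the width of the primary interval and in the interaction test. The interaction powers also assume 300 evaluable patients, a 10-point interaction, equal obesity groups and a common baseline slope. Nothing can be claimed about the size of the gain from the strata.

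**What to change.** In the Analytic approach section, or in the SAP if it is already settled there, specify or confirm the following:

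1. The primary model is a linear regression of six-month WOMAC function (or, equivalently for the treatment effect, its change) on arm, baseline WOMAC function, age group, sex and surgeon-volume stratum. Report the adjusted mean difference with its 95% CI.
2. The subgroup test uses the same model plus obesity and the arm-by-obesity term.
3. The unadjusted comparison of changes is kept as a sensitivity analysis.

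The cost is wording only. Baseline WOMAC is collected at the preoperative visit and the three stratification factors are known at randomization, the day after surgery. The change score already needs the baseline value, so no further patient is lost. The estimand in Outcome measures does not change. The wording should be settled before outcome data are examined by arm, so that the choice between adjusted and unadjusted results is not made afterwards.

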### Data management

We managed study data in REDCap (Research Electronic Data Capture), a secure, web-based application designed to support data capture for research studies
[18]. Data were entered into the REDCap database and exported to SAS version 9.2 for statistical analysis (SAS Institute, Cary NC). The hard copy questionnaires and medical chart abstractions are kept on site in a locked file cabinet.

The REDCap calendar function alerted study staff to follow-up questionnaires due to be sent. The follow-up window for the three and six month questionnaires were ± two weeks and ± four weeks, respectively. Mailings to patients included a cover letter, the follow-up questionnaire, and a pre-paid envelope with the BWH address preprinted for easy return. If a patient's questionnaire was not received within two weeks of the mailing, study staff made up to four phone calls to the patient to inquire on the status of the questionnaire. Data from returned questionnaires were immediately entered into the REDCap database and a remuneration check of $25.00 was issued to the study participant. If no contact was made with the patient and the questionnaire was not received by the end of the event window, the questionnaire was listed as not returned.

## Discussion

The AVIKA Navigator study was designed to address a critical question related to successful delivery of TKA: whether support from persons trained in motivational interviewing techniques leads to a more efficient and satisfactory rehabilitation process post-TKA, as measured by improvements in functional status between baseline and six months, and whether such support is particularly beneficial in persons with concomitant comorbidities, including obesity. The study is set to enroll 345 subjects in a tertiary clinical center between August, 2010 and December, 2013. This will be the largest clinical trial to date to examine the efficacy of a motivational-interviewing-based strategy to improve recovery following TKA. The cost-effectiveness analysis planned alongside the trial will address questions regarding the value of the intervention, as well as its budgetary impact for hospitals and payers. Given drastic increases in the utilization of TKA, efforts to improve recovery while controlling resource utilization are critical to ensure the clinical and economic value of TKA.

## Abbreviations

TKA: Total knee arthroplasty; OA: Osteoarthritis; MI: Motivational interviewing; AViKA: Adding Value in Knee Arthroplasty; RCT: Randomized controlled trial; BWH: Brigham and Women’s Hospital; LMR: Longitudinal medical record; ESP: Electronic surgical plan; IRB: Institutional review board; WOMAC: Western Ontario and McMaster Universities Osteoarthritis Index; REDCap: Research Electronic Data Capture.
